### Statistical methods

In accordance with the intention-to-treat (ITT) principle, incomplete data will be collected, and reasons for missing data should be presented clearly so that the statistician can handle missing data with the appropriate statistical approach.

In general, all original data extracted from our online custom-designed database will be analyzed with SPSS Statistics version 22.0 software by a statistician. Continuous variables with a normal distribution will be expressed in the form of mean ± standard deviation, while continuous variables with a non-normal distribution or ordinal variables in the form of medians (with lower and upper quartiles), and categorical variables will be described as counts and proportions. To detect the statistically significant difference between the two groups, the independent sample *t* test will be performed for measurement data, the χ^2^ test for categorical data, and the Mann-Whitney *U* test for data that conform to an abnormal distribution. Any reported *p* value (two-sided) less than 0.05, with 95% confidence intervals, will be interpreted as the indication of a statistically significant difference.

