## Methods

### Study design and setting

Developed according to the Standard Protocol Items: Recommendations for Interventional Trials (SPIRIT) Statement [8] (the SPIRIT checklist is shown in Additional file 1), this trial will be a randomized, two parallel-armed, patient- and assessor-blinded study conducted in three centers (Shanghai Pudong Hospital of Traditional Chinese Medicine (TCM), Longhua Hospital affiliated to Shanghai University of TCM, and Baoshan Hospital of Integrated Traditional Chinese and Western Medicine) in Shanghai from December 2018 to November 2021. Research results will be reported consistent with Consolidated Standards of Reporting Trials (CONSORT) guidelines [9] and the Revised Standards for Reporting Interventions in Clinical Trials of Acupuncture (STRICTA) [10]. A flowchart of this trial procedure is shown in Fig. 1. This RCT has been approved by the Ethics Committee of Shanghai Pudong Hospital of TCM on 11 October 2018, meaning all interested participants will sign a written informed consent form (see Additional file 4) with a clear understanding of the purpose, study procedure, and all potential risks of this trial. All written informed consent forms will be collected and obtained by the chief coordinator.

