### Sample size

The sample size calculation is conducted based on the result of a conventional therapy RCT [11], in which the post-treatment ODI score ($$ \overline{x} $$ ± S) decreased to 26.29 ± 18.02 in the intervention group, and 34.58 ± 15.10 in the control group. It is indicated that, in the condition of α = 0.05 (two-sided) and 1 – β = 80%, the sample size of our proposed study should be 128 (64 for each group). Allowing for a sample loss of 20%, the final sample size is inflated to 160 in total with a 1:1 allocation ratio.

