### Outcome measures

The assessments consist of two self-assessment instruments and a physician-based questionnaire (all Chinese versions) in addition to a routine medical history review and physical examination. Assessments will be performed before allocation at screening (T0, baseline), a week after the final treatment (T1, primary endpoint), 13 weeks after the final treatment (T2, secondary endpoint), and 25 weeks after the final treatment (T3, final endpoint). The timeframe of data collection and assessments is shown in Fig. 2 (the SPIRIT figure).

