#### Primary outcome measure

The primary outcome measure is the change in the ODI. The ODI involves 10 questions which mainly evaluate pain severity, self-sufficiency level, and quality of daily life [14]. Each question is calculated from 0 to 5 and then added up into an overall score. The higher the overall score is, the worse the general condition.

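### The sample size is built on the SD of post-treatment ODI, but the primary outcome is change in ODI and only unadjusted tests are named; ANCOVA on baseline ODI would remove the mismatch at no cost

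*Protocol article*

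**What the plan says.** Four sections of the protocol article bear on this.

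- **Primary outcome measure:** "The primary outcome measure is the change in the ODI".
- **Outcome measures:** "Assessments will be performed before allocation at screening (T0, baseline), a week after the final treatment (T1, primary endpoint"). Baseline ODI is therefore scheduled for every participant before randomization.
- **Sample size:** the inputs are post-treatment ODI results from another trial, which "decreased to 26.29 ± 18.02 in the intervention group, and 34.58 ± 15.10 in the control group". With these, "in the condition of α = 0.05 (two-sided) and 1 – β = 80"%, the article concludes that "the sample size of our proposed study should be 128 (64 for each group"), raised to 160 for 20% loss. It states no SD of change, no baseline SD and no correlation between baseline and follow-up.
- **Statistical methods:** between groups, "the independent sample *t* test will be performed for measurement data", a chi-squared test is used for categorical data, and Mann-Whitney is the "test for data that conform to an abnormal distribution". No model with baseline ODI as a covariate appears.

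**The concern.** The variable that was sized (ODI after treatment) is not the variable declared primary (change in ODI). Randomization makes the expected group difference the same on both scales, but the standard deviation is generally not the same. The 80% therefore belongs to a different analysis from the one described, and the reader cannot tell what power the described one has.

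Two further points follow. Baseline ODI enters only by subtraction, which fixes its coefficient at 1. Estimating the coefficient, as ANCOVA does, is at least as precise. And if the observed distribution decides between the t test and Mann-Whitney, the primary effect measure (a mean difference or a rank shift) is not settled before the data are seen. The 8.29-point planning difference corresponds only to the mean difference.

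At stake are the precision of the trial's main result and the clarity of what it estimates.

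**Working it through.** **Inputs from the article.** Post-treatment means 26.29 and 34.58; SDs 18.02 and 15.10; two-sided alpha 0.05; power 80%; 64 per group.

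**Inputs not in the article, so assumed.** The baseline-to-T1 correlation ρ (range 0.2 to 0.7) and the baseline SD, SD0 (equal to the T1 SD first, then 12 and 20).

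**Step 1: reproduce the stated size.**
- Difference = 34.58 − 26.29 = 8.29.
- Pooled SD at T1, SD1 = √[(18.02² + 15.10²)/2] = √276.37 = 16.62. Standardized difference = 8.29/16.62 = 0.499.
- n per group = 2 × (1.960 + 0.842)² × 276.37/8.29² = 63.1, rounded up to 64.
- 128/0.8 = 160.

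The stated figures reproduce. Exact noncentral-t power at 64 per group is 79.9%. This is the power of a t test on T1 scores.

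**Step 2: when does the same power apply to change?**
- Var(change) = SD0² + SD1² − 2ρ·SD0·SD1.
- Setting this equal to SD1² gives ρ = SD0/(2·SD1).
- With equal SDs the break-even is 0.5. With SD0 = 12 it is 12/33.25 = 0.36. With SD0 = 20 it is 20/33.25 = 0.60.

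Above the break-even the change-score test has more than the planned power, and below it less.

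**Step 3: ANCOVA.**
- Residual variance = SD1²(1 − ρ²), which does not depend on SD0.
- Var(change) − Var(ANCOVA) = SD0² − 2ρ·SD0·SD1 + ρ²·SD1² = (SD0 − ρ·SD1)², which is never negative.

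So ANCOVA is at least as precise as the change score at every correlation and every baseline SD. The extra degree of freedom it uses is immaterial at this size.

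**Step 4: power at 64 per group, difference 8.29, equal SDs of 16.62 (noncentral t).**

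| ρ | SD of change = 16.62·√[2(1 − ρ)] | Power, t test on change | ANCOVA SD = 16.62·√(1 − ρ²) | Power, ANCOVA |
|---|---|---|---|---|
| 0.2 | 21.03 | 60.0% | 16.29 | 81.5% |
| 0.3 | 19.67 | 65.8% | 15.86 | 83.5% |
| 0.4 | 18.21 | 72.4% | 15.24 | 86.3% |
| 0.5 | 16.62 | 79.9% | 14.40 | 89.8% |
| 0.6 | 14.87 | 87.9% | 13.30 | 93.8% |
| 0.7 | 12.88 | 95.1% | 11.87 | 97.5% |

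Evaluable n per group for 80% power at ρ = 0.3, 0.5 and 0.7: 90, 65 and 39 for the change score; 59, 49 and 34 for ANCOVA.

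**Step 5: vary the baseline SD at ρ = 0.3.**
- SD0 = 12: SD of change = √(144 + 276.37 − 119.69) = 17.34; power about 77%.
- SD0 = 20: SD of change = √(400 + 276.37 − 199.49) = 21.84; power about 57%.
- ANCOVA is 83.5% in both cases.

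Even at ρ = 0, ANCOVA has 79.9%, the figure that the plan was sized for.

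**The case against.** **No shortfall is demonstrated.** This stands. A reader might infer from the lower rows of the table that the trial is underpowered. The article does not support that. It gives neither ρ nor the baseline SD, and above the break-even correlation the change-score test exceeds 80%. The entry rule of VAS ≥ 5 could narrow the baseline spread and lower the break-even, but nothing in the article says by how much.

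**The declared test is not wrong.** This also stands. A t test on change is unbiased over randomization and keeps its type I error. Chance baseline imbalance is already part of the variance of change, so it is not a second harm on top of the loss of precision.

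**Adjustment is commonly left to an analysis plan.** This stands in part. The Statistical methods section speaks in general terms, does not name ODI at T1 and does not rule out a further model. But the finding is not just that detail is missing. The article states the primary variable, the sizing inputs and the tests, and the sizing does not match the variable. An unseen plan that adjusted for baseline would resolve the analysis, and the sample-size paragraph would still need to say which variable it sizes.

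**Centre.** The design is a "patient- and assessor-blinded study conducted in three centers", and a reader might infer that the analysis must adjust for centre or acupuncturist. The Randomization section describes no stratification, so there is no design factor that obliges it. Such a term is optional.

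**Choice of test by distribution.** None of the power figures bears on this. It is a point about fixing the estimand in advance, and no size is claimed for it.

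**Conclusion.** The mismatch is real. The 64 per group is arithmetically right for post-treatment ODI, while the declared primary variable is change in ODI, and the only between-group tests named for continuous data are unadjusted. The stated 80% carries over to a t test on change only if ρ is about SD0/(2·SD1).

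With equal SDs of 16.62, a true difference of 8.29 and 64 evaluable per arm, the declared analysis has about 66% power at ρ = 0.3 and 95% at ρ = 0.7. ANCOVA has about 84% and 98%. If the baseline SD is 12 or 20 instead, change-score power at ρ = 0.3 is about 77% or 57%. All of these rest on assumed values of ρ and the baseline SD.

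The conclusion is limited to this: the power statement is attached to the wrong variable, and a more efficient analysis is available from data already scheduled. It is not that the trial is too small or the test invalid. Severity: SHOULD-FIX.

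**What to change.** - Name the primary analysis as ANCOVA of ODI at T1 on treatment and baseline ODI, reporting the adjusted mean difference with its 95% confidence interval whatever the observed distribution.
- Keep Mann-Whitney as a sensitivity analysis only.
- Use the same model, each with its own baseline, for VAS and the JOABPEQ lumbar items, and at T2 and T3.
- State in the sample-size paragraph that the calculation is for the T1 score, so that ANCOVA keeps about 80% power or more at any correlation under the planning assumptions. If the t test on change is kept instead, justify the size with an SD of change, or with an explicit correlation and baseline SD.
- A term for centre may be added but is not required.

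The cost is wording in the protocol or analysis plan, settled before unblinded analysis. It needs no new data and no extra patients, and the SPSS software already named fits the model.

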## Discussion

In China, warm acupuncture is regarded as an upgraded acupuncture treatment for lumbosacral radiculopathy (LR) because of its combined therapeutic effect of both acupuncture and thermal therapy. It is assumed that the infrared rays introduced by the heat source can improve the blood circulation and enhance cell phagocytosis [17], leading to a strong anti-inflammatory effect around the responsible nerves [18], complete with the non-specific effect of acupuncture: the excitement of the endogenic opioid system [19].

According to thermology, the higher the temperature of an object is, the stronger the infrared rays it emits. Therefore, we assume that, for a warm acupuncture procedure, the thermal conducting property of the needle is essential, for it might influence the heat transfer and thus change the intensity of infrared rays so that, to some extent, it affects the clinical efficacy.

A study group [20] revealed that a silver needle, with seven times more heat transferred into the acupoints and the affected site, is superior to the most commonly applied stainless steel filiform type. This may be a potential explanation why, as reported in another recent study [21], silver-needle warm acupuncture could reduce the expression of neuronal nitric oxide synthase (nNOS) and substance P (SP) and increase the expression of 5-HT in the spinal cord [22], generating an analgesic effect [23].

An additional advantage in this proposed study is that we adopt an electrothermal moxibustion-imitating apparatus with a specially designed heat pipe to heat the needles. Compared to the conventional warm acupuncture procedure that uses burning moxa, which usually causes heavy smoke and burn injuries, the electrical heating device is feasible to avoid any unpleasant scent or air pollution. More importantly, according to the result of our pilot study, it can minimize the risk of burn injury by controlling the temperature at a relatively safe level. Thus, good patient compliance can be ensured.

### Trial status

Recruitment of participants started on 12 December 2018 and is anticipated to end on 30 June 2020. (The protocol is Version 1.0, dated 2018/12/1.)

## Data Availability

All data generated or analyzed in this study will be fully available without restriction through the online platform of the Chinese Clinical Trial Registry.

## Abbreviations

CAM: Complementary and alternative medicine
CEQ: Credibility/expectancy questionnaire
CRF: Case Report Form
DSMB: Data and Safety Monitoring Board
ITT: Intention-to-treat
JOABPEQ: Japanese Orthopedic Association Back Pain Evaluation Questionnaire
LDH: Lumbosacral disc herniation
LR: Lumbosacral radiculopathy
nNOS: Neuronal nitric oxide synthase
ODI: Oswestry Disability Index
Qol: Quality of life
RCT: Randomized controlled trial
SP: Substance P
SPIRIT: Standard Protocol Items: Recommendations for Interventional Trials
STRICTA: (Revised) Standards for Reporting Interventions in Clinical Trials of Acupuncture
TCM: Traditional Chinese medicine
VAS: Visual analog scale
